## Abstract

**ABSTRACT:**

**Introduction:**

Hepatocellular carcinoma (HCC) is a leading cause of cancer-related mortality, and mortality rates have continued to rise despite advancements in treatment. Six-monthly ultrasound surveillance is recommended by professional bodies for early detection of HCC in high-risk cohorts. However, surveillance rates remain poor; only 20% of patients attend for regular surveillance. Population health outreach strategies may be able to enhance surveillance rates by addressing patient-related barriers to engagement with healthcare. Using a co-design approach, we have developed outreach material in tandem with patients, with the aim of boosting HCC surveillance. VIGILANT aims to compare the effectiveness of bespoke mailed surveillance invitations with or without patient navigators (PNs) in improving attendance rates at surveillance appointments.

**Methods and analysis:**

This is a two-arm randomised controlled trial that will recruit 652 participants. Participants will be patients with chronic liver disease or cirrhosis, who are eligible for HCC surveillance as defined by criteria from the National Institute for Health and Care Excellence and European Association for the Study of the Liver. Participants will be randomised (in a 1:1 ratio) to receive either (a) a mailed surveillance invitation or (b) a mailed invitation plus telephone call reminder from a PN 1 week prior to the appointment. The primary objective is to evaluate the impact of PNs and mailed invitations on attendance rates. Secondary objectives include rates of diagnosis of early-stage HCC among patients undergoing surveillance and cost-effectiveness of each arm.

**Ethics and dissemination:**

Approval has been sought to conduct the research from Aberdeen Research Ethics Committee (REC Reference: 335338). The study is sponsored by Imperial College London and funded by RM Partners (West London Cancer Alliance). Study findings will be presented at medical conferences and published in peer-reviewed journals.

**Trial registration number:**

NCT06635694.

STRENGTHS AND LIMITATIONS OF THIS STUDYPragmatic randomised controlled trial design enabling evaluation of the effectiveness of studied interventions in a real-world setting.This trial adopted a co-design process in designing the mailed surveillance invitations disseminated to patients to place patients’ needs at the crux of the proposed interventions—a novel approach not previously used in hepatocellular carcinoma (HCC) surveillance studies.Study targets an ethnically diverse patient population, increasing applicability to regions across the UK.The use of outreach media may exclude marginalised and deprived populations that are typically hard-to-reach and disproportionately represented in the HCC surveillance target population.

## Introduction

 Hepatocellular carcinoma (HCC) is the third leading cause of cancer-related death globally.^1^ Mortality rates in the UK have tripled in the last 50 years and are projected to increase by 10% in the forthcoming two decades.^2^ Despite advancements in treatment, prognosis remains poor, with 5 year survival rates below 15%.^3^ One of the main drivers of poor prognosis is the detection of HCC at an advanced stage, precluding patients from curative therapy; over 75% of patients do not receive treatment with curative intent due to late stage diagnosis.^4^

Cirrhosis is a major risk factor for the development of HCC and is present in up to 90% of patients.^5^ Current guidelines from the European Association for the Study of the Liver (EASL), American Association for the Study of Liver Diseases and National Institute for Health and Care Excellence (NICE) recommend liver surveillance in patients with chronic liver disease with 6 monthly abdominal ultrasound scans to improve rates of early diagnosis and, consequently, improve survival outcomes.^6 7^ Despite recommendations, HCC surveillance is underused worldwide; in Europe, less than 50% of eligible patients receive surveillance.^8^ A recent meta-analysis in 2022 consisting of 29 studies yielded a pooled estimate of only 24% of patients with cirrhosis undergoing surveillance.^8^

Factors contributing to low surveillance uptake are manifold and may be broadly classified into patient-related, provider-related and system-level aspects.^8 9^ Several patient-related factors have also been identified, such as challenges with test scheduling, difficulty travelling to appointments and lack of understanding of the need for surveillance.^10 11^ Our work suggests that lack of knowledge and fear act as key barriers to HCC surveillance attendance.^12^ Understanding the reasons for surveillance failure allows for the development of more targeted interventions.

In the UK, current provision of HCC surveillance is ad hoc—eligible patients are identified and booked for a 6 monthly ultrasound scan by their designated clinician (usually a gastroenterologist, hepatologist or hepatology clinical nurse specialist). Patients receive an ultrasound appointment in the post, with no formal invitation or information about the surveillance test. We adopted a co-design process using workshops involving patient advocates with lived experience of liver disease and liver health charity representatives to identify barriers to surveillance attendance. Co-design is a collaborative approach, often employed in health service research, which actively involves stakeholders and service users to develop more effective solutions to a pre-specified problem.^13^ Reported barriers and patient preferences were subsequently used to develop user-friendly invitations and informational material.^12^ Focus groups also discussed telephone patient navigators (PN) as an additional intervention that may increase surveillance uptake.

Freeman *et al* describe eight key principles of PN, which highlight crucial considerations in designing the PN service, such as outlining a clear job scope for the navigator, ensuring cost-effectiveness and employing an individual with skills commensurate with the demands of the role.^14^ In line with these principles, PN is best delivered through establishment of a one-to-one relationship between a patient and navigator; the navigator being a trained staff member who can serve as a longer-term contact person working with the patient to identify and overcome hurdles in their individualised circumstances to access healthcare.

PN has been widely described as an effective intervention in enhancing participation rates for a wide range of screening programmes including breast, cervical, HCC and colorectal cancer, though these studies have been predominantly based in the USA.^15^ Two recent large-scale randomised controlled trials (RCTs) by Singal and colleagues have shown that mailed outreach and PN significantly improve HCC screening rates. Yet, in both studies, overall uptake remained poor, with less than 30% of at-risk patients receiving recommended biannual surveillance scans.^16 17^ A key limitation of these studies was the lack of co-design in developing mailed outreach material, which may render the intervention less relevant to the target population.

There has been no research to date on interventions developed through co-design aimed at improving HCC surveillance rates. The VIGILANT study aims to address this issue.

## Methods and analysis

### Study design

VIGILANT is a RCT with two parallel groups, aiming to investigate the effect of mailed invitations with or without PN to improve the rate of HCC surveillance uptake over 2 years. Adults aged ≥18 years, at risk of developing HCC and suitable for HCC surveillance will be eligible to participate in the study. Surveillance uptake will be quantified based on patients’ attendance at their surveillance imaging appointments. In standard clinical practice in the UK, patients receive a random appointment time and date through the post, with subsequent provisions to reschedule if they are unable to attend the initial proposed appointment. To investigate the effect of enhanced outreach, trial participants will be randomised to one of the two following arms using a computer-generated number (figure 1):

Bespoke surveillance invitation, consisting of a one-page mailed invitation and an informational postcard.Bespoke surveillance invitation plus PN, which comprises a scripted PN telephone call 1 week prior to surveillance appointment (in the event of non-attendance, a further follow-up PN call).

**Figure 1 F1:**
[figure not shown]
Flowchart of overall study timeline, allocation to trial arms and outcome measures. HCC, hepatocellular carcinoma.

### Development of intervention measures

The mailed outreach material used in both trial arms, along with the patient navigation strategies, was iteratively designed in collaboration with patients, advocacy groups and behavioural specialists through workshops. Using the COM-B (Capability, Opportunity, Motivation) model of behaviour, we systematically mapped experiences shared by workshop participants to each component of the framework to identify key barriers that would need to be addressed through the study interventions. This facilitated the development of the letter invitation for HCC surveillance and the creation of a supplementary informational postcard accompanying the letter. Insight into the barriers faced by patients to participating in surveillance also shaped the content and structure of the script for telephone navigation.^12^

### Trial objectives

#### Primary objective

The primary objective is to evaluate the effect of bespoke mailed invitations and the addition of PN on the rate of patient attendance at surveillance appointments at each 6 monthly interval over a 2 year period.

#### Secondary objectives

Rate of diagnosis of early-stage HCC in each trial arm will be assessed and compared. A cost-effectiveness analysis will be undertaken to determine whether the introduction of PN in addition to bespoke mailed invitations to boost uptake of HCC surveillance is economically viable.

### Eligibility criteria

Participants will be recruited from a local patient database held by the liver care team at Imperial College Healthcare NHS Trust. A generic screening process will be undertaken through electronic chart review where the following data items will be collected: patient age, patient sex, home address postcode, whether the patient is a native English speaker and aetiology of liver disease. The database will only be accessed by the direct care team to identify potential trial participants.

Subjects will need to be deemed eligible for HCC surveillance as defined by NICE and EASL guidelines. This includes adults with liver cirrhosis classified as Child–Pugh A or B, and cirrhotic patients with Child–Pugh C disease awaiting liver transplantation.^18^ Comprehensive inclusion and exclusion criteria are outlined in table 1.^7^ The study aims to recruit 652 eligible participants.

**Table 1 T1:** Inclusion and exclusion criteria

Inclusion criteria	Exclusion criteria
Age ≥18 years	Known previous or current diagnosis of HCC
Good or moderate performance status (ECOG, category 0–2)	Patients with Child–Pugh stage C cirrhosis who are not a candidate for liver transplantation
Child–Pugh stage A or stage B cirrhosis	Previous liver transplant
Child–Pugh stage C cirrhosis, awaiting liver transplantation	Score of >7 on the Clinical Frailty Scale
Non-cirrhotic chronic hepatitis B patients at intermediate or high risk of HCC (according to PAGE-B classes for Caucasian subjects, respectively 10–17 and ≥18 score points)	

ECOG, Eastern Co-operative Oncology Group; HCC, hepatocellular carcinoma.

The study will run between 2 January 2025 and 2 July 2027, and participant recruitment commenced on 1 February 2025.

### Study procedures

Study participants will be randomised into one of the two trial arms:

Mailed invitations only.PN in addition to mailed invitations.

Randomisation will be carried out centrally using a computer-generated sequence. Concealed allocation will be used to reduce the risk of selection bias. Due to the nature of the interventions, no blinding will be employed.

The current surveillance recommended by NHS England comprises regular 6 monthly liver ultrasound scans for eligible patients.^7^ In routine clinical practice, the surveillance ultrasound scan will be requested by the subject’s responsible clinician. Ensuing ultrasound appointments will be flagged and booked by the clinical team using a bespoke call-and-recall system (RedCap).

#### Mailed invitations

Participants will be sent a formal invitation letter, endorsed by the patients’ general practitioner (GP), and an informational card via post to their home address (see online supplemental appendix 1). The mailed information leaflet will provide written and illustrative information on the ultrasound screening process and address frequently asked questions, including duration of the scan and level of discomfort. Two weeks prior to the ultrasound appointment date, patients will receive a reminder either via text message or letter. Following the scan, results will be automatically communicated to the patients’ hepatology care team and GP. Patients will also receive a copy of the results through mail or the ‘Patients Know Best’ app and be invited for a repeat ultrasound scan in 6 months if the scan is normal. In the event of an abnormal ultrasound scan, the patient will be contacted by their direct care team to organise further investigations.

Non-attendance will be followed by a further mailed invitation for their next surveillance appointment. In the event of failure to attend two appointments, the patients’ GP will be informed, and the patient will be contacted by their direct care team to explore reasons for non-attendance. The study process for participants in this trial arm is summarised in figure 2.

**Figure 2 F2:**
[figure not shown]
Flowchart of study procedures for participants allocated to trial arm receiving mailed invitations only. GP, general practitioner.

#### Patient navigation

PNs are staff members who are already part of the patient’s existing direct care team (eg, usually a Band 4 administrator). For the purposes of this study, a specific staff member will be recruited to fulfil this role. Patients randomised to this trial arm will receive a mailed invitation plus a scripted telephone call from a PN (see online supplemental appendix 2). Patients will receive a telephone call from a PN 1 week prior to their surveillance appointment to (i) remind the patient of the appointment, (ii) offer to reschedule the appointment if the patient is unable to attend and (iii) address any concerns about the appointment. Additionally, PNs will call patients who have failed to attend a surveillance appointment to explore any barriers to attendance and offer solutions as to how these might be addressed. In the event of failure to attend two appointments, the patients’ GP will be informed, and the PN will call the patient to explore and record reasons for non-attendance. The study process for participants in the PN trial arm is summarised in figure 3.

**Figure 3 F3:**
[figure not shown]
Flowchart of study procedures for participants allocated to trial arm receiving patient navigation. GP, general practitioner.

### Outcomes

The primary outcomes of the study are (i) attendance rates at each 6 month interval and (ii) proportion of patients in each trial arm attending HCC surveillance regularly. Frequency of attendance at surveillance scans will be categorised into three groups: regular, infrequent and non-attendance.

Regular attendance is defined as fulfilment of four or more HCC surveillance episodes over the study period, with no more than 8 months interval between surveillance appointments.Infrequent attendance is defined as attendance at some HCC surveillance appointments, but less than four episodes, or with intervals greater than 8 months between surveillance appointments.Non-attendance is defined as no attendance at any HCC surveillance appointments over the study period.

Secondary outcome measures are (i) proportion of patients in each arm diagnosed with early-stage HCC compared with late-stage HCC and (ii) comparative cost of interventions.

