### Data collection

Data collected during the study will be recorded on REDCap, a secure web-based application for databases. Attendance at surveillance scans and HCC outcomes will be entered onto the database. At the end of the study (2 years), the following data will be extracted for analysis: age, sex, ethnicity, native language, Index of Multiple Deprivation quintile (based on patient’s home postcode), aetiology of liver disease, surveillance episodes, diagnosis of HCC and reasons for removal from surveillance pathway, if any.

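### The regular-attendance primary outcome counts four scans in a study period with no stated start for each participant, so a patient who attends everything within the 8-month limit can be classed as infrequent

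*Protocol article*

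**What the plan says.** The Outcomes section names two primary outcomes: attendance at each 6-month interval, and the proportion attending regularly. For the second it says: "Regular attendance is defined as fulfilment of four or more HCC surveillance episodes over the study period, with no more than 8 months interval". The 8 months are counted between surveillance appointments. The next category takes everyone who attended something but fell short: "Infrequent attendance is defined as attendance at some HCC surveillance appointments, but less than four episodes", or whose intervals were too long. Neither category refers to how many appointments the patient was offered.

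The length of the study period appears in two forms. The Primary objective speaks of attendance "at each 6 monthly interval over a 2 year period", Study design also gives 2 years, and Data collection says "At the end of the study (2 years), the following data will be extracted for analysis". Eligibility criteria gives calendar dates: "The study will run between 2 January 2025 and 2 July 2027, and participant recruitment commenced on 1 February 2025". The article states neither when recruitment ends nor when the first appointment falls after randomisation.

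On scheduling, Mailed invitations says that patients will "be invited for a repeat ultrasound scan in 6 months if the scan is normal". Under Patient navigation, the call one week before the appointment includes an "offer to reschedule the appointment if the patient is unable to attend".

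**The concern.** A fixed count of four makes sense only if every participant has the same opportunity to reach four. Here that opportunity depends on two things other than attendance: how long after entry the first appointment falls, and how far each booking slips past 6 months. If the next scan is invited 6 months after the last one, a late scan moves all later ones, and the slippage adds up.

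The wording on gaps errs in the other direction. If the 8 months run between appointments and not between completed scans, a patient can miss a scan and still satisfy the rule.

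At stake is the meaning of a primary outcome. Some true regular attenders would be moved into the infrequent group for reasons of booking, which shrinks the absolute difference between arms. The trial is unblinded, so a choice of window made after attendance is visible by arm would be open to challenge.

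**Working it through.** **Inputs.** At least four scans and gaps of at most 8 months (Outcomes); a 24-month window (Study design, Primary objective, Data collection); calendar dates 2 January 2025 to 2 July 2027, which is 30 months, or 29 from the start of recruitment (Eligibility criteria); next scan 6 months after a normal one (Mailed invitations); 326 per arm, 10% baseline, 10-point difference, alpha 0.05 (Sample size and power calculation). The first-scan month m and the actual gaps are not in the document and are assumed below.

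**1. Are the conditions compatible?** Yes. Four scans at exact 6-month gaps span 3 × 6 = 18 months and fit 24 months for any first scan up to month 6. Three 8-month gaps span 3 × 8 = 24 months and fit only if the first scan is at month 0.

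**2. When does a patient who never misses fall short?** Four scans fit a window of W months if m + g1 + g2 + g3 ≤ W, that is, if the mean gap is at most (W − m)/3.

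| First scan, month m | W = 24 | W = 30 |
|---|---|---|
| 0 | 8.0 | 10.0 |
| 1 | 7.67 | 9.67 |
| 3 | 7.0 | 9.0 |
| 6 | 6.0 | 8.0 |

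Example with W = 24: scans at 6, 13 and 20, next due at 27. All gaps are 7 months and nothing is missed, but there are only three scans. With W = 30, four scans fit for every m from 0 to 6, even at 8-month gaps.

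**3. How often (assumed timing)?** Take m uniform over 0–6 and gaps uniform over a range with mean g, all within 6–8 months. Averaging over m, P(fewer than four in 24 months) = (3g − 18)/6.
- Gaps 6–6.5 (g = 6.25): 0.75/6 = 12.5%.
- Gaps 6–7 (g = 6.5): 1.5/6 = 25%.
- Gaps 6–8 (g = 7): 3/6 = 50%.

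Simulation agrees. If the clock starts at the first offered appointment and that appointment is kept, m = 0 and the figure is 0% in all three cases.

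**4. The gap wording.** Suppose appointments at 0, 6, 12, 18 and 24, with the scan at 6 missed (assuming the next appointment stays at 12; the article gives no timing after a missed visit). Appointments are 6 months apart and four scans are completed, so read literally the patient is regular. Between completed scans the first gap is 12 months, so the patient is infrequent.

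**5. Consequence for power.** The plan's own figure first: 326 per arm, 10% vs 20%, two-sided pooled z-test, gives 94.9%, not the stated 85%. That mismatch is a separate matter. If a share s of true regular attenders is retained equally in both arms, the difference becomes s × 10 points. For s = 0.75, 7.5% vs 15%:
- null SE = √(2 × 0.1125 × 0.8875/326) = 0.02475
- alternative SE = √((0.075 × 0.925 + 0.15 × 0.85)/326) = 0.02458
- z = (0.075 − 1.96 × 0.02475)/0.02458 = 1.08, so power is 86%.

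The same formula gives 91% at s = 0.875 (8.75% vs 17.5%) and 68% at s = 0.5 (5% vs 10%). The result depends on the base rate: a true 20% vs 30%, which the protocol does not state, starts at 84% and falls to 69% at s = 0.75.

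**The case against.** A reader might infer that the definition contradicts itself. It does not: step 1 shows that both conditions can be met together, and a patient scanned exactly 6-monthly from any start up to month 6 is regular. The 8 months cap a single gap and are not a target average, so tolerating one late scan while asking for roughly 6-monthly attendance is a coherent choice.

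A reader might also infer that 2 years and 30 calendar months cannot both be right. They can: the dates are compatible with staggered entry followed by 24 months each, since entry on 2 July 2025 leaves exactly 24 months. What stands is that the rule says study period without saying which clock it means, and the answer changes the classification. The timeline figure was not available and may show more.

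A third inference is that rescheduling by the navigator biases the outcome against that arm. The documents do not support a direction. Study design says that ordinary practice also allows rescheduling, and a rescheduled appointment may turn a missed scan into a completed one, which helps that arm. No gap lengths by arm are given.

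Finally, the accumulation of delays assumes that the 6 months run from the last scan. On a fixed 6-monthly grid delays would not accumulate, and the example at 6, 13 and 20 would not arise. The wording in Mailed invitations favours the first reading but does not settle it. The other primary outcome does not use the four-scan rule at all.

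**Conclusion.** The point holds as a badly fixed definition of one of two primary outcomes. In a 24-month window from randomisation, the rule can class a fully attending patient as infrequent, and its gap wording can class a patient with a missed scan as regular. The article gives the definition in full, so this is more than detail left to another document.

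The size is not known. The 12.5% to 50% range rests on an assumed even spread of first scans over 0–6 months, on assumed gaps, and on delays that accumulate; it falls to zero if the window starts at a first appointment that is kept, or if it is 30 months long. Loss of true regular attenders at the same rate in both arms shrinks the absolute difference but leaves the ratio of proportions unchanged. On the protocol's own rates, a 25% loss leaves 86% power, still above the stated 85%, so the power argument alone is not decisive. The stronger reason to act is that the outcome would partly measure appointment timing.

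**What to change.** Keep the four-scan minimum and the 8-month limit, and change the clock and the unit:

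- Count scans in one fixed 24-month window per participant, starting at the date of the first offered appointment. Scans at 0, 8, 16 and 24 months then qualify. Use the offered date and not the attended date, because attendance is itself the outcome.
- Measure the 8 months between completed scans.
- Replace the undefined study period in Outcomes with this window, and reconcile it with Study design, Primary objective, Data collection and the calendar dates in Eligibility criteria.
- Record the change before attendance is analysed by arm.
- Report, by arm, how many participants have less than the full 24 months by 2 July 2027. Do not excuse scans due after that date as not yet due, because required scans would then again depend on entry date.

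The cost is the redefinition of one derived variable and a short amendment, provided that REDCap holds the dates of offered appointments and completed scans; no patient's care changes. Two limits remain. Participants first offered an appointment after 2 July 2025 will not reach 24 months by the study end date, and their number cannot be told from the article. And if the first scan is completed r months after the first offered date, the limit on the mean gap is (24 − r)/3, so the problem is much reduced but not wholly removed.

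### Primary outcome (ii) classes participants whose surveillance ends before four episodes, through HCC, transplant or death, as infrequent or non-attenders even if they attended every scan offered

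*Protocol article*

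**What the plan says.** The protocol article (Outcomes) names two primary outcomes: (i) attendance at each 6-month interval and (ii) the proportion attending regularly. For (ii) it defines three groups:

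- Regular: "Regular attendance is defined as fulfilment of four or more HCC surveillance episodes over the study period", with gaps of no more than 8 months.
- Infrequent: "Infrequent attendance is defined as attendance at some HCC surveillance appointments, but less than four episodes", or gaps above 8 months.
- Non-attendance: "Non-attendance is defined as no attendance at any HCC surveillance appointments over the study period".

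The Primary objective sets attendance "at each 6 monthly interval over a 2 year period", so about four scans fall due, or five if a month-0 scan counts.

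Other sections show that some participants will leave surveillance:

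- Table 1 (Eligibility criteria) excludes "Known previous or current diagnosis of HCC" and previous liver transplant, yet it admits patients who are awaiting a transplant.
- Under Mailed invitations, patients will "be invited for a repeat ultrasound scan in 6 months if the scan is normal". Otherwise, "In the event of an abnormal ultrasound scan, the patient will be contacted by their direct care team to organise further investigations".
- Data collection lists "diagnosis of HCC and reasons for removal from surveillance pathway, if any" among the items to be extracted.

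Statistical analysis specifies an intention-to-screen approach.

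**The concern.** The three groups are exhaustive and depend only on the count and spacing of attended scans. Nothing separates a participant who stopped attending from one for whom surveillance was no longer due. A fully adherent participant diagnosed at the first, second or third attended scan has at most three episodes and is scored infrequent. Someone who dies or is transplanted before any scan is scored as a non-attender. On a plain reading of intention-to-screen, both stay in the denominator of outcome (ii) as failures. The reasons for removal are collected but play no part in the definition.

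What is at stake is first the meaning of the endpoint. It is offered as a measure of attendance behaviour, yet it also absorbs cancer detection, transplantation and death. A reader of the results could not tell how much of the infrequent group reflects disengagement. Second, moving would-be regular attenders out of the regular group shrinks the absolute difference between the arms.

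**Working it through.** **Inputs from the article.** 326 per arm, 1:1 allocation, alpha 0.05 (taken as two-sided), 10% baseline, 10-point difference, stated power 85% (Sample size and power calculation). **Assumptions.** The article gives no rate for HCC, abnormal scans, transplant or death, so all exit rates below are assumed and shown as ranges.

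**Step 1: the plan's own figure.** With n = 326, p1 = 0.10, p2 = 0.20 and mean 0.15:

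z = [0.10 × √326 − 1.96 × √(2 × 0.15 × 0.85)] / √(0.10 × 0.90 + 0.20 × 0.80) = (1.806 − 0.990) / 0.500 = 1.63, so power = 94.9%.

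The stated 85% is not reproduced; 85% needs 228 per arm. An unstated 30% inflation would explain the number (228 / 0.70 = 325.7, rounded up to 326), but the article does not say so. This is a separate matter. The 94.9% serves here only as the reference without exits.

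**Step 2: exits from any cause, at the same share f in both arms.** Observed regular rates become 0.10(1 − f) and 0.20(1 − f):

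| f | Observed rates | Difference | Power |
|---|---|---|---|
| 0 | 10.0% vs 20.0% | 10.0 points | 94.9% |
| 5% | 9.5% vs 19.0% | 9.5 points | 93.6% |
| 10% | 9.0% vs 18.0% | 9.0 points | 92.1% |
| 20% | 8.0% vs 16.0% | 8.0 points | 88.3% |

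The ratio of the two rates stays at 2.0; only the absolute difference shrinks.

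**Step 3: exits triggered by an attended scan.** Let r be the chance that any one of scans 1-3 ends surveillance. A would-be regular attender is lost with probability q = 1 − (1 − r)³. The number reclassified is 326 × 0.10 × q in one arm and 326 × 0.20 × q in the other:

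| r per scan | q | Reclassified per arm | Excess | Difference | Power |
|---|---|---|---|---|---|
| 1% | 2.97% | 1.0 vs 1.9 | 1.0 | 9.7 points | 94.2% |
| 2% | 5.88% | 1.9 vs 3.8 | 1.9 | 9.4 points | 93.4% |
| 5% | 14.26% | 4.7 vs 9.3 | 4.7 | 8.6 points | 90.7% |
| 10% | 27.10% | 8.8 vs 17.7 | 8.8 | 7.3 points | 84.8% |

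At 1-2% per scan the excess in the higher-attending arm is about one to two people. It becomes material only at about 5% or more.

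**Step 4: which scans matter.** If scans fall at months 6, 12, 18 and 24, a diagnosis at month 18 comes at the third episode and bars the participant from the regular group. If a month-0 scan counts, month 18 is the fourth episode and does not.

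**The case against.** The strongest reply is that this is a condensed article and that a fuller protocol or analysis plan may say how removals enter the analysis; collecting the reasons suggests some intention to use them. That would settle the matter if the article were silent. It is not: it prints a complete three-way rule, and the rule as printed misclassifies these participants.

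It can also be said that counting every randomised participant is a recognised conservative choice, and that a while-eligible rule conditions on events after randomisation. That stands, and it is why neither rule should be reported alone.

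Four stronger readings are tempting and are not supported:

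- *The rule works systematically against the navigation arm.* This follows arithmetically only for exits triggered by an attended scan, and only if that arm attends more. Deaths and transplants need not differ by arm.
- *An abnormal scan ends the chance to be regular.* Mailed invitations ties the 6-month repeat to a normal scan and sends the rest for further investigation. It does not say that surveillance stops, or whether later imaging counts as an episode. A delayed return could breach the 8-month limit, but that is a possibility only. The HCC exclusion in Table 1 is an entry criterion, not a removal rule.
- *Power is seriously damaged.* Starting from the 20% regular attendance in the Abstract and adding 10 points, power falls from 84.0% to 81.5% at 5% exits and 72.5% at 20%. The sample-size section, however, plans on 10% versus 20%, where power stays above the stated 85% across that range.
- *The whole primary outcome is affected, or the trial's purpose contradicted.* The four-episode rule governs only outcome (ii). No denominator is printed for outcome (i), so nothing can be shown there. Early-stage HCC is credited as a secondary outcome.

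**Conclusion.** The point holds for primary outcome (ii). As printed, the definition scores a participant whose surveillance ends before four episodes as infrequent or as a non-attender, whatever their adherence, although the information to separate them is already collected. This is chiefly a fault of validity and interpretation.

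Its numerical effect is modest and toward zero: 10.0 points becomes 9.5-8.0 points and power goes from 94.9% to 93.6-88.3% for assumed exits of 5-20%. The arm-specific part is about one to two extra people at an assumed 1-2% scan-triggered exit per scan. These sizes rest on assumed exit rates, a two-sided test, the article's 10% versus 20%, and exits that strike would-be regular attenders alike in both arms. The classification problem itself depends on none of them. It should be corrected, but it does not threaten the trial.

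**What to change.** Before end-of-study data extraction, amend the definition of outcome (ii):

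1. Judge regular attendance against the surveillance episodes due while the participant is alive and eligible, up to the earliest of 24 months, HCC diagnosis, transplant, death or documented removal. State whether a month-0 scan counts among the episodes due.
2. Place participants who exit before any scan is due in a separate category, not in non-attendance.
3. State whether imaging after an abnormal scan counts as an episode for that 6-month window.
4. Report exits by reason and arm.
5. Report the present four-or-more rule in all randomised participants alongside.

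The cost is a change of wording and one data item, the date of removal, beside the reason already collected. The trial is unblinded, so the rule should be fixed and dated before results by arm are examined.

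The downside is real. Early leavers need fewer scans to be regular (one diagnosed at the first scan would qualify after a single attendance), and exit may itself depend on arm. That could favour the higher-attending arm, just as the present rule works slightly against it. Showing both analyses lets the reader see whether the conclusion depends on the choice.
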